# TIGA-CUB – manualised psychoanalytic child psychotherapy versus treatment as usual for children aged 5–11 years with treatment-resistant conduct disorders and their primary carers: study protocol for a randomised controlled feasibility trial

**DOI:** 10.1186/s13063-017-2166-2

**Published:** 2017-09-15

**Keywords:** Randomised controlled trial, Psychoanalytic child psychotherapy, Conduct disorders, Treatment-resistant, Inter-generational attachment

## Abstract

**Background:**

The National Institute for Health and Care Excellence (NICE) recommends evidence-based parenting programmes as a first-line intervention for conduct disorders (CD) in children aged 5–11 years. As these are not effective in 25–33% of cases, NICE has requested research into second-line interventions. Child and Adolescent Psychotherapists (CAPTs) address highly complex problems where first-line treatments have failed and there have been small-scale studies of Psychoanalytic Child Psychotherapy (PCP) for CD. A feasibility trial is needed to determine whether a confirmatory trial of manualised PCP (mPCP) versus Treatment as Usual (TaU) for CD is practicable or needs refinement. The aim of this paper is to publish the abridged protocol of this feasibility trial.

**Methods and design:**

TIGA-CUB (Trial on improving Inter-Generational Attachment for Children Undergoing Behaviour problems) is a two-arm, pragmatic, parallel-group, multicentre, individually randomised (1:1) controlled feasibility trial (target *n* = 60) with blinded outcome assessment (at 4 and 8 months), which aims to develop an optimum practicable protocol for a confirmatory, pragmatic, randomised controlled trial (RCT) (primary outcome: child’s behaviour; secondary outcomes: parental reflective functioning and mental health, child and parent quality of life), comparing mPCP and TaU as second-line treatments for children aged 5–11 years with treatment-resistant CD and inter-generational attachment difficulties, and for their primary carers. Child-primary carer dyads will be recruited following a referral to, or re-referral within, National Health Service (NHS) Child and Adolescent Mental Health Services (CAMHS) after an unsuccessful first-line parenting intervention. PCP will be delivered by qualified CAPTs working in routine NHS clinical practice, using a trial-specific PCP manual (a brief version of established PCP clinical practice). Outcomes are: (1) feasibility of recruitment methods, (2) uptake and follow-up rates, (3) therapeutic delivery, treatment retention and attendance, intervention adherence rates, (4) follow-up data collection, and (5) statistical, health economics, process evaluation, and qualitative outcomes.

**Discussion:**

TIGA-CUB will provide important information on the feasibility and potential challenges of undertaking a confirmatory RCT to evaluate the effectiveness and cost-effectiveness of mPCP.

**Trial registration:**

Current Controlled Trials, ID: ISRCTN86725795. Registered on 31 May 2016.

**Electronic supplementary material:**

The online version of this article (doi:10.1186/s13063-017-2166-2) contains supplementary material, which is available to authorized users.

## Background

Conduct disorders (CD) are ‘repetitive and persistent patterns of antisocial, aggressive or defiant behaviour that amount to significant and persistent violations of age-appropriate social expectations’ [1]. They affect 5% of 5–10-year-olds (187,500 children in England and Wales, based on 2011 census data), with prevalence expected to rise [2, 3]. Pre-adolescent CD risk particularly adverse outcomes, including poor educational achievement, teenage pregnancy, substance abuse, criminality, long-term physical and mental illness, unemployment, homelessness, domestic violence, and poor subsequent parenting [4–13]. Children’s CD impact substantially on the NHS, constituting 30% of GP child consultations and 45% of child community health referrals [1]. Long-term public service costs can be ten times higher (£70 k) for those with childhood CD than for those without, and related crime costs £22.5 billion annually [14–18]. CD are, therefore, an important, expensive, and growing problem.

There is clear evidence that many parenting programmes deliver effective outcomes [1]. However, our scoping study, funded by the National Institute of Health Research (NIHR) Flexibility and Sustainability Funding (FSF) and conducted in five Child and Adolescent Mental Health Services (CAMHS) (*n* = 145)([name], [name]. Scoping study in regional CAMHS in the north of England on children aged 5-11 with conduct disorders, unpublished) showed that evidence-based protocols are often not followed. Children and Young People’s Improving Access to Psychological Therapies (CYP-IAPT – a national programme which aims to develop an improved CAMHS) should help with this, but even evidence-based programmes do not benefit 25–33% of families, and 30–40% drop out [1, 19, 20]. The long-term costs of treatment-resistant CD are extremely high, and if parent training fails, there are few alternatives. Cognitive-behavioural and/or social learning programmes are only recommended for children aged 9+ years [1], and multisystemic interventions only for children aged 11+ years [1]. These options either involve a major component of parent training, which will already have failed for our intended patient group, or demonstrate small effect sizes, suggesting that these options will be unsuitable for treatment-resistant CD, or are more resource-intensive and intended for older children [1]. National Institute for Health and Care Excellence (NICE) has, therefore, requested research on urgently needed, second-line treatments [1].

Psychoanalytic Child Psychotherapy (PCP) for treatment-resistant CD is supported by theoretical and pragmatic research as well as by clinical experience. Large meta-analyses on links between attachment and children’s CD have found correlations between insecure (and particularly, disorganised) attachment and subsequent behaviour problems [21–24]. Other studies have found links between children’s CD and primary-carer (particularly maternal) attachment difficulties [25–28], and between children’s disorganised attachment and parental trauma [29]. Both secure and insecure attachment are liable to inter-generational transmission [29], with one meta-analysis finding a match between mother and child secure-insecure attachment styles of 75% (*κ* = .49) [30]. In our scoping study of children with behaviour difficulties in CAMHS, 60% of mothers indicated potential inter-generational attachment difficulties ([name], [name]. Scoping study in regional CAMHS in the north of England on children aged 5-11 with conduct disorders, unpublished). These are linked to problems in reflective functioning, i.e. understanding behaviour in terms of underlying thoughts and feelings [31, 32], and to adult mental health problems [33, 34], which can contribute to children’s CD [1, 35]. Nevertheless, secure attachment can be ‘earned’ via positive experiences post infancy [36–38]. Child and Adolescent Psychotherapists' (CAPTs’) clinical experience that families of children with CD often have inter-generational attachment difficulties is thus endorsed by both theoretical and empirical research.

It is widely accepted that CAPTs address highly complex problems – including inter-generational attachment difficulties – where first-line treatments have failed [39, 40]. CAPTs are trained to work with children and their primary carers, to recognise adult mental health difficulties, and to refer parents/carers to GPs and adult services, where appropriate [41]. There have been several small studies of PCP for CD. A retrospective study of children in intensive and non-intensive psychotherapy (*n* = 763) including children with CD found that 49% of children overall made clinically significant improvements in levels of functioning on the Hampstead Child Adaptation Measure (HCAM) [42], while a retrospective case-control study comparing children with a disruptive disorder (*n* = 135) and those with an emotional disorder found significant improvement in functioning in both the disruptive and emotionally disordered groups [43]. A naturalistic study (*n* = 9) found similar improvements in overall functioning and externalising behaviour using the Global Assessment of Functioning scale (GAF) and the Child Behavior Checklist (CBCL) and CBCL Teacher Report Form (CBCL-TRF) [44]. A controlled trial (*n* = 26) resulted in clinically significant improvements on the Impairment Score for Children and Adolescents (IS-CA) in 31% of children, compared with 8% in the waiting list control, but no significant difference on the CBCL [45]. A randomised controlled trial (RCT) (*n* = 69) found Family Therapy and Child Psychotherapy equally superior to the recreational control treatment group using the CBCL [46]. However, these studies all had small samples and were not conducted in UK CAMHS.

The PCP intervention used in the TIGA-CUB (Trial on improving Inter-Generational Attachment for Children Undergoing Behaviour problems) feasibility study is a systematic, manualised, brief version of existing clinical practice. It comprises 12 sessions for the child and 12 sessions for the primary carer (and any other of the child’s parents/carers who wish to attend). The term ‘primary carer’ denotes the adult – i.e. parent or kinship carer – the parents/carers consider to be the most involved in parenting the child. The ‘change hypothesis’ is that a regular, predictable, and intensive positive attachment experience with the CAPT for the child is likely directly to improve the child’s behaviour, and that direct work with the primary carer and any other parent/kinship carer who wishes to attend is likely to enhance parental reflective functioning [47, 48], improving understanding of the emotional distress that the child is communicating via the problematic behaviour [44, 49]. The work is also likely to empower primary carers, making them feel less stressed, and to help them gain greater control over parenting behaviour through understanding their own experiences of having been parented and of how their child’s behaviour might trigger their own complex and possibly traumatic childhood memories [50]. The intervention might also begin to assist primary carers to acknowledge mental health difficulties and to access adult services, where appropriate [40]. It is anticipated that primary carer benefits will result in a more sympathetic approach to the child to which the child will respond, thereby promoting a positive cycle of change.

This paper describes the protocol for the feasibility trial evaluating manualised Psychoanalytic Child Psychotherapy (mPCP) compared with Treatment as Usual (TaU) within CAMHS. In the absence of a clear evidence base at the time of our scoping study and when funding was obtained, TaU tended to be highly heterogeneous, including interventions which ranged from generic non-specific parent or child work and parenting programmes through to Play Therapy, Family Therapy, and non-manualised, long-term PCP. Our comparator is, therefore, heterogeneous TaU rather than a specific, homogeneous alternative, both because the latter is not currently practicable in CAMHS, and because one or even two comparators would answer the explanatory, but not the pragmatic, question of interest to the NHS.

### Aims and objectives

The aims of this trial are:To assess the feasibility of conducting, andTo inform the design of, a large-scale, confirmatory RCT of second-line mPCP versus TaU for children aged 5–11 years with treatment-resistant CD and their primary carers, so as to improve the range of treatment options and long-term outcomes for this hard-to-treat patient group.

The objectives of the trial are:To establish procedures for screening children referred to, or re-referred within, CAMHS with CD and their primary carers, and to estimate the recruitment rate and the proportion of primary carers with mental health difficultiesTo assess acceptability to clinicians and primary carers of randomising to mPCP or TaU.To collect baseline and 4-month blinded follow-up data (and 8-month follow-up data for those recruited in the first 4 months of the trial), to estimate likely follow-up rates and data quality for the confirmatory trialTo collect data on treatments received within CAMHS across trial arms to characterise co-interventions and TaU over timeTo assess the feasibility of, and best methods for, collecting data from various sources (primary carers, children, and teachers), including national routine data sets as they become available during the lifetime of the trialTo assess the feasibility of, and best methods for, collecting adverse events relating to the child or primary carerTo identify the most appropriate way to collect quality of life and cost data to assess short and long-term cost-effectivenessTo assess the feasibility of keeping researchers blinded, by monitoring the rate and reasons for unblindingTo establish procedures for assessing treatment attendance and adherence to the interventionTo confirm the variability and clustering of outcomes by clinician to inform sample size calculations for the confirmatory trial.

The full protocol (version 3.2, 20 April 2017) is available on request from the corresponding author.

## Methods and design

### Design

TIGA-CUB is a multicentre, two-arm, pragmatic, parallel-group, individually randomised controlled feasibility trial. A summary of the trial design is included as a flow diagram below (see Fig. 1).

**Fig. 1 Fig1:**
[figure not shown]
TIGA-CUB trial flow diagram

### Setting

CAMHS in (1) Bradford and Keighley, (2) Dudley and Walsall, (3) Sheffield, and (4) Wakefield and Castleford were selected to participate to maximise generalisability and to provide a good test of the feasibility of recruitment. Service configurations vary considerably across these settings, with all CAMHS using a triage system on first referral, but with different subsequent internal pathways, and with some CAMHS having only one CAPT while others have up to five.

### Eligibility criteria

Participant eligibility will be assessed in stages. Inclusion and exclusion criteria will first be assessed by CAMHS practitioners involved in screening referrals. The final two exclusion criteria (primary-carer alcohol and drug dependence) will be assessed by the researcher when contacting participants who have consented to researcher contact, as will confirmation of a clinical level of CD.

Inclusion criteria:Child aged 5–11 years old at baselinePresenting to CAMHS, or re-referred within CAMHS, with a clinical level of CD ≥ 4 on the Strengths and Difficulties Questionnaire (SDQ) [51] conduct subscaleChild’s current primary carer has been offered a first-line group or individual parenting programme or other structured parenting intervention in primary care or within CAMHS, involving a series of structured sessions focussing on parenting and/or child behaviour management techniques, and has attended at least one session, but the child’s CD persists and the child has been referred to CAMHS or re-referred within CAMHS for further treatment.

Exclusion criteria:Child with a clinical diagnosis of autistic spectrum disorder (ASD), including Asperger’s syndromeChild with a clinical diagnosis of severe learning difficulties (LD)Child medicated for attention deficit hyperactivity disorder (ADHD), unless they have been on a stable medication dose for 3 months or more (children with un-medicated ADHD are eligible if other inclusion criteria are met)Looked After Child (LAC), unless they are in a stable (at least 6 months) kinship adoption, kinship foster care or kinship special guardianship relationship with their carerChild under/at risk of safeguarding or court proceduresChild whose primary carer has severe mental health difficulties, determined by usual CAMHS procedures using clinical judgement (baseline General Health Questionnaire (GHQ-12) [52] will be monitored for primary carers with severe mental health difficulties not identified by CAMHS)Sibling has been randomised to TIGA-CUB (avoidance of potential contamination)Primary carer is actively receiving a parenting programme within CAMHS for the child’s siblingPrimary carer lacks capacity to comply with trial requirements, e.g. as a result of a LD, or due to insufficient proficiency in EnglishPrimary carer is currently participating in another research project that would mean participation in TIGA-CUB would be too burdensomePrimary carer has severe adverse parental functioning, e.g. alcohol dependence (≥20 on Alcohol-Use Disorders Identification Test) (AUDIT-C) [53] or drug dependence (≥ 3 on the Drug Abuse Screening Test) (DAST-10) [54], determined by the trial researcher on initial screening visit.

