### Participant identification and recruitment

Due to CAPT clinical practice and availability, it is anticipated that recruitment will take place in line with school terms and half terms where possible, resulting in recruitment of up to five cohorts of participant dyads during the recruitment period. Recruitment will be initiated after referral to, or re-referral within, CAMHS. All referrals aged between 5 and 11 years with a potential CD will be screened. Once a potential primary carer-child dyad has been identified and CAPT capacity has been confirmed, the local CAMHS practitioner will introduce the trial to them. If the primary carer is interested in participating, the primary carer and child will be provided with TIGA-CUB Information Leaflets and consent will be gained for initial researcher contact. In addition, as part of the process evaluation for the trial, primary carers will receive a questionnaire gauging their understanding of the trial and asking about their views on the recruitment process, and will be asked if they would be willing to consent to a process evaluation researcher contacting them subsequently to collect more detailed feedback. Responses will be reviewed so that recruitment processes can be refined for a confirmatory trial.

Where consent is given for initial researcher contact, the primary carer will be contacted and a meeting scheduled either at the primary carer’s home or at another appropriate location to explain the trial in greater detail, establish full trial eligibility, obtain consent, and undertake the baseline assessment. The dyad will have been given at least 24 h to read and digest the Information Leaflets previously provided, and will have had the opportunity to discuss them with their family and/or other health care professionals (e.g. GP) if they so wish, before being asked whether they would be willing to take part in the trial.

All primary carers will be asked to complete the AUDIT-C and DAST-10, plus the SDQ. Formal consent will not be required prior to completion of these measures, as completion will constitute implied consent. Those who decline at this stage will be offered TaU for their child. Those who complete these measures but score outside of the thresholds specified in the inclusion criteria will not be eligible to take part, and will also be offered TaU.

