## Abbreviations

ACP: Association of Child Psychotherapists
ADHD: Attention deficit hyperactivity disorder
ASD: Autistic spectrum disorder
AUDIT-C: Alcohol-Use Disorders Identification Test
BNF: *British National Formulary*
CAMHS: Child and Adolescent Mental Health Service
CAPT: Child and adolescent psychotherapist
CBCL: Child Behavior Checklist
CBCL-TRF: Child Behavior Checklist-Teacher Report Form
CD: Conduct disorders
CI: Confidence interval
CNA: Could not attend
CTRU: Clinical Trials Research Unit
CYP-IAPT: Children and Young People’s Improving Access to Psychological Therapies
DAST-10: Drug Abuse Screening Test
DNA: Did not attend
EQ-5D: EuroQol 5 Dimensions
EQ-5D-Y: EuroQol 5 Dimensions Youth
FSF: Flexibility and Sustainability Funding
GAF: Global Assessment of Functioning
GHQ-12: General Health Questionnaire
GP: General practitioner
HCAM: Hampstead Child Adaptation Measure
HRA: Health Research Authority
ICC: Intracluster correlation coefficient
IS-CA: Impairment Score for Children and Adolescents
ISRCTN: International Standard Randomised Controlled Trial Number
ITT: Intention-to-treat
LAC: Looked After Child
LAG: Lay advisory group
LD: Learning difficulties
mPCP: Manualised Psychoanalytic Child Psychotherapy
NHS: National Health Service
NICE: National Institute for Health and Care Excellence
NIHR: National Institute for Health Research
PCP: Psychoanalytic Child Psychotherapy
PPI: Patient and Public Involvement
PSI: Parenting Stress Index
PSSRU: Personal Social Services Research Unit
QALY: Quality-adjusted Life Year
RCT: Randomised controlled trial
REC: Research Ethics Committee
RfPB: Research for Patient Benefit
RUSAE: Related and unexpected serious adverse event
SAE: Serious adverse event
SD: Standard deviation
TaU: Treatment as Usual
TIGA-CUB: Trial on Improving Inter-Generational Attachment for Children Undergoing Behaviour problems
TMG: Trial Management Group
TSC: Trial Steering Committee.

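### The carer alcohol exclusion pairs a cut-off of ≥20 with the AUDIT-C, a form that under standard scoring cannot reach 20, so the instrument name and threshold must be reconciled

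*Protocol article*

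**What the plan says.** In the protocol article, the last item of the exclusion list (Eligibility criteria) concerns carers with "severe adverse parental functioning, e.g. alcohol dependence" or drug dependence. The alcohol threshold is written as "alcohol dependence (≥20 on Alcohol-Use Disorders Identification Test) (AUDIT-C"). The opening of the same section assigns the check: "The final two exclusion criteria (primary-carer alcohol and drug dependence) will be assessed by the researcher".

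Participant identification and recruitment names the form to be completed: "All primary carers will be asked to complete the AUDIT-C and DAST-10, plus the SDQ". It then makes the scores decisive: "Those who complete these measures but score outside of the thresholds specified in the inclusion criteria will not be eligible to take part". That sentence points to the inclusion criteria, but the alcohol and drug thresholds appear only under the exclusion criteria, so I read it as covering them.

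Table 1 lists the AUDIT-C as carer-completed, at screening only, and lists no other alcohol measure. The abbreviation note to Table 1 and the Abbreviations section both expand the label with the name of the parent test, the latter as "AUDIT-C: Alcohol-Use Disorders Identification Test". The number of items, the points per item and the score range are not given anywhere.

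**The concern.** The suffix C denotes the short consumption form of the Alcohol-Use Disorders Identification Test, whereas a threshold of 20 suits a longer scale. A screening rule whose threshold lies above the maximum score of its instrument excludes nobody.

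Two things would then be at stake.

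- **The exclusion itself.** Carers whom the trial means to exclude for alcohol dependence could pass the researcher's score check and be randomised.
- **What the feasibility trial hands on.** Screening procedures are part of the first objective (Aims and objectives). Point and interval estimates of the eligibility rate are meant to inform the confirmatory trial (Statistical analysis). A count of zero exclusions on the alcohol score would be fixed by the rule, yet could be read as evidence that carer alcohol dependence is rare in this population.

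**Working it through.** The check is whether the threshold is attainable. No sample size, power or precision figure is involved, and the article has no figure of its own to reproduce beyond the cut-off.

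**Inputs from the article**
- Cut-off: ≥20 (Eligibility criteria).
- Instrument named: AUDIT-C, in Eligibility criteria, Participant identification and recruitment, Table 1, the note to Table 1, and Abbreviations.
- Other alcohol instruments or cut-offs: none.

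**Inputs assumed (not in the article)**
- AUDIT-C: 3 items, each scored 0–4.
- Full test: 10 items, each scored 0–4.

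**Formula:** maximum score = number of items × maximum points per item, compared with 20.

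| Form given | Maximum | Against 20 | Effect on the alcohol-score rule |
|---|---|---|---|
| AUDIT-C | 3 × 4 = 12 | 20 − 12 = 8 points short | Cannot be met; 0% of carers excluded on this score |
| Full test | 10 × 4 = 40 | 20 is on the scale | Can be met; the instrument is misnamed |

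**How far the result depends on the assumption.** For a three-item form to reach 20, an item would need 20 / 3 = 6.67 points on average, so at least 7 points per item if all items share one integer maximum. The assumed 4 would have to be wrong by a wide margin.

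**Whether the text decides between the two rows.** It does not. The label always carries the C suffix, which points to the short form. The expansion is always the parent test's name, which points the other way, but only weakly. The article also drops the number when it expands DAST-10 (Drug Abuse Screening Test) and, in the note to Table 1 and in Abbreviations, GHQ-12 (General Health Questionnaire). A missing form identifier in an expansion is therefore this article's habit and does not show that the full test was meant.

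**The case against.** The strongest reply is that this is a slip in a label. The decisive figure, a maximum of 12, is not in the article. Every expansion gives the full test's name, and on that test 20 is attainable. The article is an abridgement, and the full protocol (version 3.2) may name the instrument correctly. Even on the worst reading only one clause fails: alcohol dependence is an example within a broader exclusion, the DAST-10 limb stands, CAMHS practitioners screen first, and the exclusions for safeguarding, severe carer mental health difficulties and lack of capacity to comply may catch some of the same carers. The trial is a feasibility study of 60 dyads without formal testing, and no estimate or success criterion changes.

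Much of this stands. A reader might infer that the exclusion can never apply, that the researcher's screen removes nobody, or that alcohol-dependent carers were in fact randomised. The article does not support any of these. The first two hold for the alcohol score only, and only if the three-item form was given. The third would need screening data that the article does not contain.

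Two parts do not stand. The score range is a fixed property of the instrument that the article names, and the conclusion is stated as conditional on it. Nor is this detail left to a fuller document: the article prints both an instrument and a cut-off, and under standard scoring they do not fit each other. The other safeguards do not replace the score either, because the article gives alcohol dependence to the researcher and ties eligibility to the thresholds.

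**Conclusion.** The concern holds in conditional form. As printed, the alcohol-score limb names an instrument and a cut-off that are incompatible under standard scoring (maximum 12 against a threshold of 20). Either the threshold is unattainable on the form given, in which case exclusions on this score are zero by construction, or the full test is given and its name is wrong throughout the article. The text does not allow a reader to tell which.

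The defect is confined to that limb. The drug-dependence limb and the wider parental-functioning criterion still operate, and no sample size or precision figure changes. How many carers would be affected cannot be estimated from the article.

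Severity is moderate. The point affects an eligibility rule and the screening data that the trial is meant to deliver, but it may prove to be only a naming error. The conclusion rests on the assumed item counts and item scores given above.

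**What to change.** Make the instrument name and the threshold agree in Eligibility criteria, Participant identification and recruitment, Table 1 and its abbreviation note, and Abbreviations, so that the cut-off lies on the scale of the form actually given. The choice of instrument and cut-off belongs to the investigators; none is proposed here.

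Recruitment was ongoing at publication (Trial status), so also confirm which form was used for the dyads already screened. If it was the three-item form, report that the alcohol-score exclusion was inoperative for them, and do not present a zero count as information on how common alcohol dependence is.

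The cost is a minor amendment. If the investigators move from the short form to the full test, carers answer up to 10 − 3 = 7 more items at screening. A working threshold may also bring a few more exclusions. If the full test was already in use, only the wording changes.
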